### Data analysis

Statistical analyses of the primary and secondary endpoints will be conducted on the intention-to-treat (ITT) population. As a sensitivity analysis, the analyses will also be performed on the per-protocol (PP) population. The primary endpoint of the improvement in VO_2_ peak after 12 weeks (t_1_) compared to baseline (t_0_) will be assessed using a one-sided two-sample *t*-test assuming equal variances at a significance level of *α* = 0.05. In addition, a linear regression will be applied, adjusting for age, sex, non-squamous vs. squamous, and FEV1. All secondary analyses, including the secondary objective, will be exploratory, meaning without adjustment of the significance level for multiplicity, and will be conducted using standard methods of statistical inference. Quantitative variables (including test scores) will be summarized by mean and standard deviation and analyzed using univariable and multivariable linear regression to detect differences between the groups. Dichotomous variables will be summarized by percentage frequencies and analyzed using a univariable and a multivariable generalized linear model with identity link in order to estimate absolute risk differences. Event times will be summarized by percentage frequencies analyzed using univariable and multivariable Cox regression, and Kaplan-Meier curves will be illustrated for event times. Subgroup analyses will be conducted based on age, gender, and first- or second-line treatment. Compensation for any study-related harm is provided through trial-specific patient insurance. Missing outcome data because of death or worsening condition will be treated as the worst case scenario. If, in addition, no more than 5% of the primary objective (or secondary objective) endpoint are missing, no additional imputation will be performed. If more than 5% of the primary objective (or secondary objective) endpoint are missing for other reasons than death or worsening, the analysis will be based on multiple imputation assuming MAR (missing at random). Details of the statistical analyses including sensitivity analyses will be specified in a Statistical Analysis Plan (SAP) prior to the start of analysis. Due to the study design with a wait-and-watch control group that later transitions into the exercise intervention, full blinding of data analysts is not feasible. However, treatment groups will be coded using neutral labels (e.g., group 1 and group 2), and analyses will be performed without access to identifiable clinical data.

The processing of NMR-based metabolomic data will be performed using an adapted version of the AlpsNMR package in R, which includes baseline correction, spectra alignment based on sodium trimethylsilylpropanesulfonate (DSS), and total intensity normalization [83]. The statistical analyses will include principal component analysis (PCA) with robust outlier detection. Loadings between |0.7| and |1| will be employed to identify the main determinants of the observed changes in the blood metabolome. The identification of the underlying substances in the PCA will be conducted using the Human Metabolome Database (https://hmdb.ca/). Furthermore, partial least squares (PLS) analysis will be used to correlate these changes in the metabolome with other clinical and biochemical parameters, thereby identifying the main drivers of plasma metabolome changes. Pearson correlation will be employed for numeric data with a linear relationship and normal distribution, while Spearman correlation will be used for rank data or non-linear relationships. Correlations between 0.7 and 1.0 (or −0.7 and −1.0) are generally considered strong, while correlations between 0.4 and 0.7 (or −0.4 and −0.7) are moderate. Correlations with a *p* value less than 0.05 are considered statistically significant.

Metabolic data analysis utilizing the R package ALPs was modified by researchers at the Children’s Hospital 2, University Hospital Essen, to meet the particular requirements of this study.

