### Randomization

Patients will be randomized into one of three study arms (arm A: endurance + resistance training, arm B: endurance training + breathing exercises, arm C: control group = usual care + exercise recommendation (following the guidelines of the American College of Sports Medicine)) using a web-based tool (https://randomizer.at). The allocation ratio is 2:1:1 for the first randomization into the control arm and two exercise arms followed by a 1:1 randomization of the original control group. Randomization is conducted after baseline assessment and is stratified based on the following two criteria to ensure balanced distribution of prognostic factors across all groups:

Histological stratification (non-squamous vs. squamous)

Squamous and non-squamous lung cancer differs by underlying biology, molecular characteristics, and response patterns to systemic therapy.

Forced expiratory volume in 1 s (FEV1)

FEV1 is a crucial measurement of lung function and is highly associated with VO_2_ peak. In advanced lung cancer patients, impairment of pulmonary function is common. FEV1 will be divided into two classifications: mild to moderate COPD—FEV1 is equal to or greater than 50% of predicted value and severe to very severe COPD—FEV1 is lower than 50% of predicted value.

The minimization method is used for stratified sampling [69]. Due to the nature of the intervention, participant blinding is not feasible. However, allocation concealment is ensured because the randomization sequence is generated and implemented through a secure, web-based system that prevents foreknowledge of group assignment. Outcome assessors conducting VO_2_ peak testing will remain blinded to treatment allocation. The randomization sequence was generated by an independent statistician. After baseline assessment, the responsible exercise scientist randomizes participants to the intervention groups using the secure, web-based randomization tool.

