### Sample size calculation

The sample size calculation is based on the primary endpoint of the improvement in VO_2_ peak after 12 weeks (t_1_) compared to baseline (t_0_). Using a study by Quist et al. [81], where VO_2_ peak was measured in patients with advanced lung cancer before and after a 6-week exercise therapy, an assumed mean difference of 0.1 is considered between the exercise therapy groups and the control group. Additionally, a standard deviation of 0.18 is assumed [80]. With a one-sided *t*-test assuming equal variances at a significance level of 0.05 and a power of 0.80, 41 patients are required in the control group and 41 patients in the exercise therapy groups. Considering that approximately 15% of deaths are expected after 24 weeks due to disease progression [82], a dropout rate of 20% is assumed, resulting in the inclusion of 52 patients per group (52 patients in the control group, 26 patients in arm A, and 26 patients in arm B). The 52 patients of the control group will also be randomized to one of the treatment arms, resulting in also 52 patients per treatment arm for the comparison of arm A vs. arm B for the secondary objective. All secondary analyses, including the secondary objective, are exploratory, so that the sample size calculation is only based on the primary objective.

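### The confirmatory t-test on change in VO2 peak adjusts for neither baseline VO2 peak nor the minimisation factors, and the supporting regression omits baseline VO2 peak: valid, but less precise than it could be

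*Protocol article*

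**What the plan says.** All references are to the Protocol article.

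- **Data analysis**, confirmatory test: "The primary endpoint of the improvement in VO_2_ peak after 12 weeks (t_1_) compared to baseline (t_0_) will be assessed using a one-sided two-sample" t-test with equal variances at alpha 0.05. No covariates are attached to it.
- **Data analysis**, supporting model: "In addition, a linear regression will be applied, adjusting for age, sex, non-squamous vs. squamous, and FEV1".
- **Randomization**: allocation takes place after the baseline assessment and uses minimisation on two factors, histology (squamous or not) and FEV1 (cut at 50% of predicted). On the second factor the article says: "FEV1 is a crucial measurement of lung function and is highly associated with VO_2_ peak".
- **Sample size calculation**: the number of patients is derived for the same unadjusted one-sided t-test on the same change score.
- **Data analysis**, missing data: outcomes missing because of death or worsening are set to a worst case. Further detail is left to a statistical analysis plan, but the primary test and the regression covariates are already named here.

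**The concern.** Two sources of precision are available and the test that carries alpha uses neither.

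First, a raw change score fixes the slope on baseline at 1. Unless the true slope is 1, part of the change is predictable from the baseline value and stays in the error term. Neither listed primary-endpoint analysis names baseline VO2 peak as a covariate.

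Second, if minimisation balances a factor that predicts the outcome and the test then omits that factor, the test's standard error is larger than the real sampling variation. The supporting regression avoids this for histology and FEV1; the confirmatory test does not.

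At stake is power and the width of the confidence interval in a trial planned at 41 evaluable patients per group. The choice is stated in the article, so this is not a gap left to the analysis plan.

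**Working it through.** **Inputs from the article.** Mean difference 0.1; SD 0.18; one-sided alpha 0.05; power 0.80; 41 evaluable per group; 20% dropout; 52 enrolled per group; control versus pooled exercise is 1:1.

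**Inputs not given, so assumed.** Rho, the correlation between VO2 peak at t0 and t1, shown from 0.5 to 0.9. Equal variances at t0 and t1. The article does not say whether 0.18 is the SD of change or of a single measurement, so both readings are shown.

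**1. The plan's own figure.** With n = 41, the noncentrality is 0.1 / (0.18 × √(2/41)) = 2.515 on 80 degrees of freedom, giving power 0.802; n = 40 gives 0.793. Then 41 / 0.80 = 51.25, rounded up to 52. Both stated figures reproduce.

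**2. Adding baseline VO2 peak, complete data.** With single-measurement variance σ²:

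- variance of change = 2σ²(1 − rho)
- ANCOVA residual variance = σ²(1 − rho²)
- ratio of the second to the first = (1 + rho)/2

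Example with 0.18 as the SD of change and rho = 0.7: residual SD = 0.18 × √0.85 = 0.166; noncentrality = 2.515 / √0.85 = 2.73 on 79 degrees of freedom; power 0.86.

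| rho | variance ratio | power at 41 per group (t-test 0.80) | n per group for 80% power (t-test 41) |
|---|---|---|---|
| 0.5 | 0.75 | 0.89 | 31 |
| 0.6 | 0.80 | 0.87 | 33 |
| 0.7 | 0.85 | 0.86 | 35 |
| 0.8 | 0.90 | 0.84 | 37 |
| 0.9 | 0.95 | 0.82 | 39 |

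**3. The other reading of 0.18.** If it is the SD of a single measurement, the SD of change is 0.18 × √(2(1 − rho)). Power at 41 per group, t-test versus ANCOVA, is then 0.80 versus 0.89 (rho 0.5), 0.94 versus 0.97 (0.7) and 0.99 versus 0.99 (0.8).

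**4. With worst-case values.** The article does not define the worst case numerically. A simulation with 41 per group gave a random 10% or 15% of patients the lowest observed change, with 0.18 as the SD of change. The gain of ANCOVA over the t-test, both under the same rule, was:

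- 10% worst-case: about 5, 3, 2 and 1 percentage points at rho 0.5, 0.7, 0.8 and 0.9
- 15% worst-case: about 4, 2 and 1 points at rho 0.5, 0.7 and 0.8, and 1 point or less at rho 0.9

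Allowing for variation between simulation runs, the gain is roughly 6 to 0 points.

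**5. Omitting the minimisation factors.** Suppose the factors are perfectly balanced and explain a share R² of the variance of change (not given). The true one-sided size of the unadjusted test is then about 1 − Φ(c / √(1 − R²)), where c = 1.664 is the critical value on 80 degrees of freedom.

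| R² | approximate true alpha | power, unadjusted | power, adjusted |
|---|---|---|---|
| 0 | 0.048 | 0.80 | 0.80 |
| 0.05 | 0.044 | 0.81 | 0.82 |
| 0.10 | 0.040 | 0.82 | 0.84 |
| 0.20 | 0.031 | 0.83 | 0.87 |

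The 0.048 in the first row is the error of the approximation itself. The direction is conservative throughout.

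**The case against.** The strongest reply is that this is a preference for a more efficient method and not an error. Endpoint, test and sample size agree with one another, and 41 and 52 reproduce. On the protocol's own assumptions the planned 80% is met. The hierarchy is also clear: the t-test decides and the regression is additional. All of this stands, and it limits the point to efficiency.

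Several stronger readings are tempting, and the document does not support them:

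- *That the trial ignores its minimisation factors.* It does not. The supporting regression adjusts for exactly those two; only the confirmatory test leaves them out.
- *That the result would be biased, through regression to the mean or otherwise.* Under randomisation, regression to the mean affects both groups equally in expectation. What remains is chance baseline imbalance, which the standard error already covers.
- *That the false-positive rate is inflated.* Omitting balanced prognostic factors makes the test conservative.
- *That the article's remark on FEV1 proves a loss.* The remark concerns the level of VO2 peak, not its 12-week change, and a change score already subtracts the level. The step 5 loss is therefore conditional on the factors predicting change, and FEV1 may add little once baseline VO2 peak is in the model.
- *That power would rise from 80% to 89%.* That figure needs rho = 0.5 and complete data. The Sample size calculation section expects about 15% deaths by 24 weeks, so some worst-case values are likely and the realistic gain is smaller.

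The reply does not remove the core: where the true slope on baseline is not 1, a covariate already collected before randomisation is left unused by both listed analyses.

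**Conclusion.** The point holds as a matter of efficiency. The confirmatory test adjusts for neither baseline VO2 peak nor histology and FEV1, and the supporting regression adds the two factors but not baseline VO2 peak.

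Under the step 2 assumptions the gain forgone is about 9 percentage points of power at rho 0.5 and 2 at rho 0.9. Under the plan's worst-case rule it is roughly 6 to 0 points, if 10–15% of patients are affected at random and receive the lowest observed change. Any gain from the minimisation factors depends on how well they predict change, which the article does not say.

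The trial is not shown to be underpowered or invalid. The change is worth making because it costs almost nothing, not because the planned test is wrong.

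**What to change.** Before analysis, and before any outcome is compared by group, amend the Data analysis section and carry the change into the statistical analysis plan:

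1. Make the primary test the one-sided group coefficient (arms A and B together versus control, alpha 0.05) from a linear model of 12-week VO2 peak, or of the change, on group, baseline VO2 peak, histology and FEV1. Age and sex are optional. State the form in which FEV1 enters.
2. Keep the unadjusted t-test as a supportive analysis.
3. State how worst-case values for death or worsening enter the model: which value is assigned, and whether on the 12-week or the change scale. With complete data and baseline in the model, both scales give the same group coefficient; with assigned values they may not. A rank-based version of the model is one option.

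The sample size of 52 per group can stand; the reduced numbers in the working illustrate the gain and are not a proposal to recruit fewer. The cost is a few sentences and no new data.

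### The sample size leaves out patients who die, but the primary t-test keeps death and worsening at a worst-case value, so the stated 80% power does not describe the planned analysis

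*Protocol article*

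**What the plan says.** All references are to the protocol article.

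Under Sample size calculation, the inputs are as follows: "an assumed mean difference of 0.1 is considered between the exercise therapy groups and the control group", and "a standard deviation of 0.18 is assumed". The test is set out as: "With a one-sided *t*-test assuming equal variances at a significance level of 0.05 and a power of 0.80". The result is that "41 patients are required in the control group and 41 patients in the exercise therapy groups". Losses are then allowed for: "Considering that approximately 15% of deaths are expected after 24 weeks due to disease progression [82], a dropout rate of 20% is assumed". This raises 41 to 52 per group (52 control, 26 in each exercise arm, 104 in total).

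Under Data analysis, the primary endpoint is the 12-week change: "The primary endpoint of the improvement in VO_2_ peak after 12 weeks (t_1_) compared to baseline (t_0_) will be assessed" by the same one-sided equal-variance t-test, on the intention-to-treat population. For losses, "Missing outcome data because of death or worsening condition will be treated as the worst case scenario". Data missing for other reasons are multiply imputed under MAR once more than 5% are missing.

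**The concern.** The two sections treat the same patients in opposite ways. In the sample size, a patient who dies contributes nothing: the allowance is a division by 0.8, and 0.1 and 0.18 describe patients with a measured change. In the analysis, that patient stays in the t-test with an extreme value.

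If such values occur about equally often in both arms, they do two things to a comparison of means. They dilute the difference, because a patient scored at the worst value shows no exercise effect. They also widen the distribution, because the values sit in the lower tail. Both reduce power. At stake is the probability that the trial's only confirmatory test detects the effect it was designed for.

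**Working it through.** **1. The plan's own figure.** Inputs: difference 0.1, SD 0.18, one-sided α 0.05, power 0.80.

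n per group = 2 × 0.18² × (1.645 + 0.842)² / 0.1² = 0.0648 × 6.18 / 0.01 ≈ 40.1, so 41. The exact noncentral t gives 40.76, also 41, with power 0.802. Allowance: 41 / 0.8 = 51.25, so 52. Both stated figures reproduce. With 20% simply left out of 52 per group, simulated power is about 80–81%. The arithmetic is sound for an analysis that omits these patients.

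**2. The effect of the analysis rule.** Let d be the share in each arm scored at worst value w, with everyone else observed and equal d in both arms.

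- Mean difference = (1 − d) × 0.1
- Variance in an arm with mean change m = (1 − d) × 0.18² + d(1 − d)(m − w)²

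Example with d = 15% and w = −0.36 (2 SD below no change; assumed):

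- Difference = 0.85 × 0.1 = 0.085
- Control variance = 0.85 × 0.0324 + 0.1275 × 0.36² = 0.0275 + 0.0165 = 0.0441
- Exercise variance = 0.0275 + 0.1275 × 0.46² = 0.0275 + 0.0270 = 0.0545
- Pooled SD = √((0.0441 + 0.0545) / 2) = 0.222, against 0.18 planned
- Standard error at 52 per group = √(0.0986 / 52) = 0.0435; 0.085 / 0.0435 = 1.95; 1.95 − 1.645 = 0.31, so power is about 62%
- n per group for 80% = 0.0986 × 6.18 / 0.085² ≈ 84.4, so 85

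The same formula with w = −0.36 gives 61, 68, 85 and 103 per group at d = 7.5%, 10%, 15% and 20%.

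**3. Range.** The article gives neither d at 12 weeks nor w, so both are assumptions. Simulated power at 52 per group (20,000 trials per cell, normal changes, one-sided pooled t-test, accurate to about one point):

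| d per arm | Worst observed change, total loss 20% | Worst observed change, others all observed | −0.36, total loss 20% | −0.36, others all observed | −0.18, total loss 20% | −0.18, others all observed |
|---|---|---|---|---|---|---|
| 5% | 69% | 76% | 71% | 78% | 78% | 84% |
| 10% | 61% | 66% | 64% | 70% | 75% | 80% |
| 15% | 55% | 57% | 58% | 62% | 73% | 75% |
| 20% | 51% | 51% | 55% | 54% | 71% | 71% |

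In the total-loss columns, the remaining losses up to 20% are taken to add no information, which approximates imputation under MAR. With the worst observed change, the SD is about 0.21 to 0.24.

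**4. Type I error.** With no true effect and d = 15% in both arms, the rejection rate is 5.1%. The rule does not inflate false positives when rates are equal.

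**5. Unequal rates.** The difference is then (1 − d_E) × 0.1 + (d_E − d_C) × w, where E is exercise and C is control. With d_C = 15%, d_E = 7.5% and w = −0.36: 0.0925 + 0.027 = 0.1195. This exceeds 0.1. With the worst observed change and 20% total loss, power in that case is about 82%.

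**The case against.** **The size of the loss depends on numbers the article does not give.** This stands. The 15% is a 24-week death figure, while the endpoint is at 12 weeks, so deaths alone may be nearer the lower end of the range, although worsening adds to them. The worst value matters as much. At −0.18 with everyone else observed, power is still at or above about 80% up to d = 10%. That is one SD below no change, a lenient worst case, but it means the shortfall is not inevitable under every reading.

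**The SAP will define the value and what counts as worsening.** Also fair: these are ordinary SAP content, and their absence here is not the point. Defining them later settles how much power is lost. It does not make the sample-size inputs match a rule the article has already fixed.

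**Exercise may reduce death or worsening.** Power could then be kept, as step 5 shows. The sample size does not assume this, and the test would then partly reflect survival or deterioration rather than VO2 peak.

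**Stronger readings a reader might infer.**

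- That any worst-case value must shrink the difference. This holds only if rates are similar in both arms or higher with exercise.
- That a patient who dies is scored at a VO2 peak of zero, or at worst in one arm and best in the other, which would cut power much further. The article says neither and gives no baseline VO2 peak.
- That losses will be labelled as worsening more readily in the supervised arms. The article does not say whose attribution decides. Weekly adverse event documentation and invitations to all assessments are not restricted to the exercise arms, and VO2 peak assessors are blinded. Differential labelling is conjecture.

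**Conclusion.** The point holds as an internal mismatch. The figures of 41, 52 and 80% are correct for an analysis that omits patients who die. The planned primary analysis keeps them, and patients missing through worsening, at a worst-case value, with the difference and SD unchanged. The 80% is therefore not the power of the stated test.

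Confidence is high on the mismatch and moderate on its size. With equal 12-week rates of 5–20% and the worst observed change, power is about 69% down to 51% with 20% total loss, or 76% down to 51% if everyone else is observed. With −0.18 it is about 78% down to 71%, or 84% down to 71%. These figures assume normally distributed changes and a true effect of 0.1 in patients with data. The problem is power; the documents give no ground for claiming excess false positives.

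**What to change.** - State the worst-case value to be used for death and worsening.
- Under that rule, recompute the expected difference, SD and power for 52 per group across a stated range of 12-week death or worsening rates, and replace the 80% claim under Sample size calculation with the result.
- Report the estimate in patients with data, with multiple imputation under MAR, as a sensitivity analysis.

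A rank-based composite, with death and worsening ranked lowest, is an option and not a required correction. It removes dependence on a chosen number, but in the same kind of simulation (20% total loss) it gives only about 53–71% and so does not restore 80%.

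The cost is a change of wording and one calculation, with no extra patients or procedures. The downside is that the stated power becomes less favourable. The article reports 25 of 104 patients enrolled, so the correction can be made well before analysis.

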**Table 2 Tab2:**
[figure not shown]
Spirit figure of the trial data collection points

^1^Check Table 1 for inclusion criteria

^2^Allocation to intervention groups will be done after completion of baseline assessment. Following randomization, strata will be used: 1. Histological stratification (non-squamous vs. squamous) and 2. Forced expiratory volume in 1 s (FEV1) >50 and under <50

^3^Randomization of the control group based on the same strata used for the first randomization

^4^Blood sampling will be done at every visit for anti-cancer treatment mostly every 3 weeks until the study ends. Cisplatin-based treatments 1 + 8 day followed by 3 weeks. Carboplatin and docetaxel d1 q3w. Blood sampling consists of BNP, high-sensitive troponin T/I as heart markers, hemoglobin [g/dl], erythrocytes [count/pl], leukocytes [count/nl], lymphocytes [count/nl], neutrophils [count/nl], C-reactive protein [mg/dl], and cytokeratin-19 fragment, CYFRA 21-1 [ng/ml]

^5^Urine (3 mL) and blood (1.5 mL) (EDTA anti-coagulated) will be collected for nuclear magnetic resonance (NMR)-based metabolome analysis

^6^Full variable of CPET consisting of forced vital capacity [L], maximal voluntary ventilation [L/min], forced expiratory volume in 1 s, one-second capacity [L], relative one-second capacity, Tiffeneau index [%], pmax [watt], HR [beats/minute], BP [mmHg], O2 saturation [%], breathing reserve [%], ventilatory threshold 1 [ml/min], ventilatory threshold 2 [ml/min], max O2 pulse [ml/beat], ventilatory equivalent for carbon dioxide slope, partial pressure in the arterial blood [mmHg], O2 partial pressure in the arterial blood [mmHg], dead space volume/tidal volume, P(A-a)O2, oxygen consumption/work load, respiratory exchange ratio (RER), pH value, PAO2 [mmHg], SaO2 [%], PCO2 [mmHg], BE [mmol/l], HCO3 [mmol/l], and SBCe [mmol/l]

^7^To be filled out by patient: EORTC-QLQ-C30—lung cancer specific LC13 and Functional Assessment of Cancer Therapy-Fatigue Scale

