### Metabolic fingerprinting

Venous blood (EDTA) and urine samples from all participants are collected at the onset of the first session and subsequently every 12 weeks until the conclusion of the study. Both sample types are subjected to centrifugation at 900 ×g at 4 °C for 10 min, and the resulting supernatant is stored at −80 °C for future analysis.

For metabolomic analysis, the samples are diluted with specific urine and plasma diluents, and sodium trimethylsilylpropanesulfonate is added as an NMR standard. NMR-based metabolomics provides a quantitative platform to profile baseline metabolic alterations in advanced lung cancer and to assess how exercise modulates systemic pathways (e.g., amino acid, lipid, and energy metabolism) in order to explore links between metabolic patterns, physiological adaptation, and clinical outcomes. Laboratory analyses are restricted to non-genetic biochemical and physiological measurements. No genomic, germline, or whole-genome analyses will be performed. Laboratory staff receive only a pseudonymized participant ID, with no access to identifiable data. All procedures follow institutional governance and quality-control standards. There is no planned future use of samples within the main study. Samples will be analyzed only for the metabolic evaluations described in the protocol, and no additional storage for other research is intended. Some patients, however, have signed a separate optional consent allowing their samples to be used in a related translational research project (e.g., potential proteomic analyses/metabolomics). Any such work will be conducted under a separate ethics approval and according to applicable governance requirements.

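### Unadjusted p < 0.05 is fixed as the label of statistical significance for the metabolite correlations, with no false discovery control and no statement that these results are hypothesis-generating

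*Protocol article*

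**What the plan says.** The NMR part of the Data analysis section describes three separate steps.

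- **PCA.** Loadings of absolute size 0.7 to 1 "will be employed to identify the main determinants of the observed changes in the blood metabolome".
- **PLS.** This method is then to relate the metabolome changes to further clinical and laboratory measurements, in the article's words "thereby identifying the main drivers of plasma metabolome changes".
- **Pairwise correlations.** Pearson or Spearman coefficients are used according to the type of data. They are graded by size: those from 0.7 to 1.0 in absolute value "are generally considered strong, while correlations between 0.4 and 0.7" are moderate. Separately, correlations with a p "value less than 0.05 are considered statistically significant". The size grade and the significance label are not tied to each other.

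Two other places bear on the status of these results. Earlier in Data analysis, all secondary analyses "will be exploratory, meaning without adjustment of the significance level for multiplicity". The Metabolic fingerprinting section gives the purpose of the NMR work as profiling metabolic changes "in order to explore links between metabolic patterns, physiological adaptation, and clinical outcomes". Neither place says how the significance label on the NMR correlations is to be read. The Objectives section does not list metabolomics.

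**The concern.** A metabolomic correlation screen pairs many features with many parameters. A per-test threshold of 0.05 flags about one null pair in twenty, however many pairs there are, so the number of chance findings grows with the screen. The plan gives each of them the same label as a real association, and it does not say how many pairs will be examined.

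What is at stake is the published account of how metabolic patterns relate to fitness, cardiac markers and clinical course. A reader who sees a list of statistically significant correlations, without the number tested or a controlled error rate, cannot judge how many to expect by chance. No treatment comparison in the protocol depends on these correlations.

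**Working it through.** **1. The plan's own figures.** The article gives no number of tests, error rate or power for the NMR analysis. The only figure to reproduce is the sample size, which sets the range of n used below. With a difference of 0.1, SD 0.18, one-sided alpha 0.05 and power 0.80:

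n per group = 2 × (1.645 + 0.842)² × (0.18/0.1)² ≈ 40.1, rounded up to 41 (t-test power at 41 per group: 0.802).

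41/0.8 = 51.25, rounded up to 52. This agrees with the article. The range is therefore n = 82 (2 × 41) to n = 104 (2 × 52).

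**2. Number of parameters.** Footnote 4 of Table 2 ("Blood sampling consists of BNP, high-sensitive troponin T/I as heart markers" and the rest of that list) gives 9 blood markers, counting troponin T/I once. Footnote 6 lists 28 CPET variables. The total is 37. Some CPET entries look like near-duplicates, so 37 is a count of listed items, not of independent quantities.

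**3. Number of pairs and expected chance findings.** The number of metabolites is not given; 20 to 100 is assumed.

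| Metabolites (assumed) | Pairs | Expected flagged if all null (0.05 × pairs) |
|---|---|---|
| 20 | 20 × 37 = 740 | 37 |
| 100 | 100 × 37 = 3,700 | 185 |

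This is for one sample type at one time point. Blood and urine are both collected, at the start and every 12 weeks. Correlation among metabolites does not alter the expected count, although it makes the actual count more variable.

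**4. Smallest correlation that passes.** The test is taken as two-sided; the article does not say. With t the 97.5% quantile on n − 2 degrees of freedom, |r| = t / √(n − 2 + t²).

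| n | Smallest significant \|r\| | p at \|r\| = 0.4 |
|---|---|---|
| 52 | 0.27 | 0.0033 |
| 82 | 0.22 | 0.0002 |
| 104 | 0.19 | 0.00003 |

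In each case the threshold lies below the plan's moderate grade of 0.4.

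**5. Share of flagged correlations that are false.** With π the share of pairs that are truly correlated:

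false share = 0.05(1 − π) / [0.05(1 − π) + power × π].

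For n = 104 and a true r of 0.3 (assumed), Fisher-z power is 0.875.

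| π (assumed) | False share |
|---|---|
| 1% | 85% |
| 5% | 52% |
| 10% | 34% |
| 20% | 19% |

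The share passes one half only when π is below 0.05/(0.05 + 0.875) = 5.4%. The document gives no basis for choosing π.

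**The case against.** The strongest reply is that the plan already declares its secondary analyses exploratory and unadjusted, and describes the metabolomics as a search for links. Unadjusted p values fit that policy, and further detail may sit in the statistical analysis plan, which is not shown. This carries some weight and lowers the severity. It does not remove the point. The exploratory clause does not name the NMR work. Even if it applies, it waives adjustment while leaving the significance label in place. Nor is the label left open for the analysis plan: the article states the rule outright.

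A second reply is that the size grading protects the reader. This stands in part. At |r| = 0.4 and n = 82, even 3,700 null pairs would give about 3,700 × 0.0002 = 0.7 chance results, and fewer at n = 104. Correlations graded moderate or strong at full sample size would thus rarely be chance. But the plan does not require that grade before it calls a correlation significant.

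A third reply is that the article never spells out a full metabolite-by-parameter screen. The clinical and biochemical parameters are named in the PLS sentence, CPET is not named there, and the PCA step might reduce what is correlated. That is fair, and it is why the counts above are conditional on assumptions.

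Two stronger readings are tempting, and the document supports neither. A reader might infer that the p < 0.05 rule decides which drivers of metabolome change are reported; in the text, the drivers come from PLS and the determinants from PCA loadings. A reader might also infer that most flagged correlations will be false. That depends on the unknown share of true associations, and step 5 gives anything from about 19% to 85%.

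**Conclusion.** The point holds in a limited form. As written, the plan labels every unadjusted metabolite correlation with p < 0.05 statistically significant, without false discovery control, without the number of tests, and without marking the results as hypothesis-generating. If all pairs were null, some 37 to 185 would be flagged; this rests on an assumed 20 to 100 metabolites crossed with all 37 listed parameters. The low bar of |r| about 0.19 to 0.22 rests only on the plan's own sample sizes and a two-sided test.

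Severity is low. The primary endpoint, its significance level, the sample size and the comparison of arms A and B are untouched.

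**What to change.** Replace the sentence on significance in the NMR paragraph with wording to this effect: *Correlations are called statistically significant only at a Benjamini-Hochberg false discovery rate of 5%, applied within each sample type (blood, urine) and time point. The number of correlations tested in each family is reported. Unadjusted p values are descriptive and hypothesis-generating.*

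The cost is one sentence and one line of R code. The downside is that fewer correlations will be flagged. The trial status section reports 25 patients enrolled by August 2025, with recruitment planned to December 2026, so the change can be made well before analysis. If the team prefers not to adjust, the minimum is to drop the significance label for these correlations and state how many were examined.
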